#### Exclusion criteria

Participation in other clinical studies is not allowed throughout the entire intervention study. Participants must not possess any food or dust mite allergies or intolerances [44, 45]. Participants who follow one or more restricted diets (veganism, gluten-free, keto, vegetarianism, etc.) or use protein supplements do not qualify for this study. Participants with gastrointestinal, kidney or liver disorders, chronic inflammation disorders (excluding obesity), and systematic antibiotic use less than 1 month prior to the study will be excluded. Diagnosed psychiatric disorders, including depression, requiring treatment can be accepted based on judgment. Participants must not be pregnant or lactating within the study period or have a self-reported use of drugs of abuse (including cannabis) within 12 months prior to the study. Participants that lack the abilities (physical and psychological) to comply with the procedures in the protocol may be excluded.

#### Recruitment

Participants will be recruited from the Copenhagen metropolitan area of Denmark. Recruitment is conducted through announcements on social media, word of mouth, flyers, and project webpage. Additionally, children of the relevant age can be requested through the Danish Civil Registration System (CPR registry) and custody holders will be invited to the study. The adult of the household will be invited to participate, to be participating together with the child, as paired participants. Recruitment rate is between 5 and 15 families a month, depending on holiday and travel seasons.

#### Randomization and blinding

Randomization will be performed in blocks of six paired participants, to assure equal allocation to the order of the two menus over the recruitment period. A computer-generated randomization list with 80 consecutive numbers will be created and stored in opaque, sealed envelopes until assigned. The allocation and enrollment is conducted by authorized site personnel. Each participant will be assigned a participant identification number (ID) and diet at the first follow-up visit. Though each participant has a unique ID, the diet will be the same for the paired participants. Participants are randomly assigned to the intervention diet by a draw from the randomized, sealed envelopes. Due to the taste and nature of the intervention foods, blinding of certain study staff and participants is not possible after the first follow-up visit. Data assessors are blinded to diet allocation.

## Measurements

### Characteristics of food perception and exposure

#### Food neophobia

All participating adults will use the Food Neophobia Scale adapted from Pliner and Hobden [46]. The questionnaire has five added questions specifically for the insect-based foods menu and will use a 7-point anchored scale (1—totally disagree and 7—totally agree). The Food Neophobia Test Tool, adopted from Pliner [47] and Damsbo-Svendsen et al. [48], will be used for all participating children using a 7-point smile scale.

#### Disgust questionnaire

All participants will complete a modified version of the food disgust questionnaire designed by Hartmann and Siegrist [49], along with additional questions that specifically apply to edible insects as adapted from Rozin et al. [50]. The original items “The texture of some kind of fish in my mouth” and “There is a little snail in the salad that I wanted to eat” from the 8-item short version of the Food Disgust scale were replaced with “To eat fish like sushi” and “There is a worm in my apple” from the 32-item Food Disgust Scale, respectively, in order to adapt to Danish culture. Adults will use a 7-point anchored scale, with 1—not disgusting at all and 7—extremely disgusting, for the main questionnaire and the anchors 1—totally disagree and 7—totally agree for the additional questions. Children will use a 7-point smile scale.

#### Exposure to edible insects

A modified exposure questionnaire adapted from Verbeke [28] is specific to insect-based foods but will be administered to all participants prior to randomization. Participating adults and children will select the statement that best applies to them. The original item “I eat insects seasonally” was changed to “I’ve tried edible insects many times” to better suit the Danish population.

#### Meat attachment

Meat attachment will be evaluated using a modified version of the questionnaire created by Graça et al. [51]. This questionnaire will only be administered to participating adults using a 7-point anchored scale (1—totally disagree and 7—totally agree).

#### End-of-study questionnaire

The end-of-study questionnaire will record participant attitude towards alternative proteins and the study products post intervention, as well as general feedback towards the organization of the study. The questionnaire will be primarily completed by the adult but will have a few short questions at the end for the adult and child to answer together as well.

### Dietary measurements

#### Four-day dietary registration

A complete 4-day dietary registration at baseline and endline will be done for all participants. The dietary registration is conducted by the use of MyFood24, a dietary web-based software available in Danish (myfood24.org).

#### Daily food records

Once the study food is distributed, the participants will be asked to keep daily records of the consumption of the intervention food using a simple online questionnaire. Participants will note if they have consumed an intervention food and to specify which and the amount consumed. They will be asked if they ate meat that dinner and, if so, to specify the type and the amount consumed.

#### Food acceptability and feedback

Participants will be asked to record their liking of two intervention foods at the first exposure (baseline) and last exposure (endline). The two products will be assigned randomly per menu.

### Other measurements

#### Household characteristics and demographics

The participating adult will fill in a questionnaire about household characteristics, including household size, ethnicity, and education. General information (age, gender, education, and ethnicity) about other household members will be collected for characterization.

#### Anthropometrics

Standard anthropometric measures (height and weight) of all participants are assessed at the first follow-up visit to be able to validate energy and protein intake recorded in the dietary registrations. Height and weight will be measured using standard procedures from the department.

#### Urine collection

Protein intake will be assessed through urine analysis using methods adapted from Yuan et al. [52]. Urea nitrogen, or carbamide, will be measured using a potentiometer (ABX PENTRA 400, Horiba Medical, Japan) and creatinine levels will be used to normalize for dilution. Spot urine samples will be taken on every other day (for a total of 3 samples) of the week prior to consuming the study foods (baseline) and during the final week of the intervention (endline). The collected urine samples will be stored in a designated research biobank and only identifiable by the assigned participant ID. We will request consent to review participants’ urine samples to assess protein intake in the current trial through the GDPR consent form. Possible excess material can be transferred to a biobank for approved, new, and related research projects if the adult and custody holders (on behalf of the child) have consented separately. Otherwise, excess materials will be destroyed.

### Data management

Documents that identify the participant will be maintained in strict confidence by the principal investigator, except to the extent necessary to allow auditing and/or monitoring by the appropriate regulatory authority and research associates. All information obtained during the study will be handled according to local regulations and GDPR by qualified personnel.

### Statistics

In order to measure the 20% replacement of meat in meals with insect- or plant- based alternatives from *x̄* = 14 meals/week to *x̄* = 11.2 meals/week, we will need a sample size of 78 paired participants. This sample size is based on *α* = 0.05, *β* = 0.80, and an assumed *σ* = 7. The standard deviation of the protein intake in the target population is uncertain and the statistical power is therefore based on assumptions. The results of the study will have important scientific value independent of the assumption of statistical power.

Statistical analysis will be used to determine changes in meal patterns as counts of meals with meat and the total protein intake at baseline and endline both within and between the insect and plant groups, hypothesizing no change in total protein intake and 20% replacement of the meat meal using linear models. The same analysis will be conducted both within and between the meat proteins with the insect-based foods at baseline and endline. A Spearman’s rho test will be used to assess perception change (neophobia, exposure, and disgust) before and after the intervention. A paired sample *t*-test (or Wilcoxon test, if not normally distributed) will be used to analyze pre- and post- intervention urine samples.

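### The 78-pair sample size does not follow from a two-sided test on its stated inputs, and it does not power the between-arm (equivalence) comparison

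*Protocol article*

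**What the plan says.** The Statistics section sizes the trial on the "20% replacement of meat in meals with insect- or plant- based alternatives", from "14 meals/week to" 11.2 meals/week. Its inputs are: "This sample size is based on *α* = 0.05, *β* = 0.80, and an assumed *σ* = 7". The result is "we will need a sample size of 78 paired participants". The article does not say whether the test is one- or two-sided, which comparison is powered, whether a pair counts as one unit or two, or whether 7 is the SD of a single measurement or of a change.

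The same section plans analyses "both within and between the insect and plant groups". Study design calls the trial a two-arm randomised equivalence trial of adult-child pairs. Randomization and blinding fixes the number: "A computer-generated randomization list with 80 consecutive numbers will be created". The Abstract also gives 80 families. With equal allocation, 78 to 80 families means 39 or 40 per arm.

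**The concern.** A reader who sees alpha 0.05 and 80% power will assume a conventional two-sided test of the trial's main comparison. The printed inputs do not lead to 78 on that assumption. The effect used is a change over time that both menus are meant to produce, whereas Objective and hypothesis says the plant arm is there to separate the effect of the insect menu from that of dietary change in general. That separation needs a between-arm comparison.

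If the paragraph stands, a non-significant difference between menus could be taken as the finding of an 80%-powered trial. Because the trial is labelled an equivalence trial, it could even be taken as evidence that the menus are equivalent.

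**Working it through.** **Inputs (Statistics section).** Difference δ = 14 − 11.2 = 2.8 meals/week; σ = 7; δ/σ = 0.40; alpha 0.05. The printed beta of 0.80 is read as power 0.80. Taken literally it means 20% power, which would need only 16 per group two-sided or 9 one-sided. Families per arm: 39 (78/2) or 40 (80/2).

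**Reproducing 78, with σ = 7 as the SD of the analysed quantity.**
Before-after in one group: n = (z_α + z_0.80)² / (δ/σ)². Two groups: twice that, per group.

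| Test | (z_α + z_0.80)² | Before-after, per arm | Two-sample, per group |
|---|---|---|---|
| One-sided | (1.645 + 0.842)² = 6.18 | 6.18/0.16 = 38.6 → 39; two arms **78** | 77.3 → **78** |
| Two-sided | (1.960 + 0.842)² = 7.85 | 7.85/0.16 = 49.1 → 50; two arms 100 | 98.1 → 99 |

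With the t distribution the one-sided figures are 40.0 and 77.97, and the two-sided figures 51.0 and 99.1. So 78 appears in the one-sided row only. It has three possible meanings there:
- 78 families per arm (156 in total);
- 78 individuals per arm, that is 39 adult-child pairs per arm and 78 pairs in total, with adult and child counted as independent;
- 39 families per arm for a before-after change whose SD is 7.

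The article does not settle which was meant.

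**Can a two-sided test reach 78?** If 7 is the SD of a single measurement and r is the baseline-endline correlation, the SD of change is 7√(2(1 − r)), and a two-sided before-after test needs 98.1 × (1 − r) families.
- r = 0.605: 98.1 × 0.395 = 38.8 → 39 per arm, 78 in total.
- r = 0.205, arms pooled: 98.1 × 0.795 = 78.0.

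Neither correlation is in the article.

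**Two-sided power at 39 families per arm, SD of analysed quantity 7.**
- Within an arm, before-after: Φ(0.40√39 − 1.960) = Φ(0.538) = 70%; 68% with t (69% at 40 per arm).
- Between arms, assuming a 2.8-meal difference, family as unit: the standard error is 7√(2/39) = 1.585. Then 2.8/1.585 = 1.766 and Φ(1.766 − 1.960) = 42%; 41% with t (42% at 40 per arm).
- The same with individuals as unit and adult and child independent (78 per arm): 70%. With assumed within-pair correlations of 0.25, 0.5 and 0.75 it is about 60%, 52% and 46%. At a correlation of 1 it returns to 41%.
- Between-arm difference detectable with 80% power, family level: 2.80 × 1.585 = 4.4; 4.5 meals/week with t. That is 4.5/2.8 = 1.6 times the whole planned fall.
- Equivalence by two one-sided 5% tests, assumed margin 2.8, true difference 0: 2Φ(1.766 − 1.645) − 1 = 10% at 39 per arm and 11% at 40. About 108 per arm would be needed for 80%.

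**If 7 is instead the SD of a single measurement** (39 families per arm, two-sided, normal approximation, assumed r):

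| r | Within arm | Between arms, change score | Between arms, baseline-adjusted |
|---|---|---|---|
| 0 | 42% | 24% | 42% |
| 0.25 | 53% | 30% | 45% |
| 0.5 | 70% | 42% | 53% |
| 0.75 | 94% | 70% | 76% |

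**The case against.** The strongest reply is that the article never claims 80% power for a 2.8-meal difference between menus. It claims it for a fall with either alternative, and it expects the insect menu to replace at least as much meat as the plant menu. This stands. A reader might infer that the plan promised 80% power between arms and delivers 41%. The text does not support that, because the 41% carries a before-after effect over to a between-arm contrast. The reply does not rescue the between-arm analysis, though. That analysis is planned, the trial is called an equivalence trial, and no sample size for that purpose is given.

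A second reply is that the meaning of SD 7 is open. A reader might infer that 78 can only be one-sided, but a suitable baseline-endline correlation gives 78 two-sided, and a high one lifts within-arm power above 80%. This also stands, but only with a correlation that the article does not state. Similarly, pooling both arms before-after gives 94% two-sided power if 7 is the SD of change. That does not match the stated 80%, and it uses no randomised comparison.

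Third, 41% is a family-level figure; counting both pair members raises it, depending on how alike they are. Fourth, the article admits that the SD is uncertain and, in the Discussion, that participants are few. Those caveats concern the SD and the size of the sample. They do not disclose the sidedness or which comparison is powered.

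**Conclusion.** The point holds in this form: the stated sample size and power do not follow from a two-sided test on the printed inputs without an added correlation. They match one-sided calculations that the article does not declare, and they do not cover the between-arm comparison. Printing beta as 0.80 is a labelling slip that does not change the result.

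With 7 as the SD of the analysed quantity, two-sided alpha 0.05 and 39 families per arm, power is about 68% within an arm. Between arms it is about 41% to 70% for an assumed 2.8-meal difference, depending on the within-pair correlation. For equivalence at an assumed margin of 2.8 it is about 10-11%. These figures are conditional on the meaning of the SD and the unit of analysis, so none is the trial's single true power. Between-arm power nevertheless stays below 80% under every assumption tabulated above.

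**What to change.** Keep the 80 families and rewrite the sample-size paragraph so that it:
- names the comparison that was powered, the sidedness of the test, and the unit (family or individual);
- says whether 7 is the SD of one measurement or of the change, and gives any correlation relied on;
- reports two-sided power recomputed under those definitions for 39-40 families per arm;
- corrects beta to 0.20 (power 0.80);
- states that the trial is not powered for the between-arm comparison, that this result will be reported by its confidence interval, and that a non-significant difference will not be read as equivalence.

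The percentages above should not be copied in until the SD and the unit are defined, because they change with those answers. The cost is one paragraph and a less favourable power statement. No extra families are needed, and the ongoing recruitment is not affected.

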#### Primary outcome

The primary outcome is the replacement of dietary meat protein with protein from the intervention foods (insect- or plant-based). The co-primary endpoints are changes in the intake of meat protein over the 6-week intervention period and the measures for replacement by the intervention products. The change is assessed as (1) change in intake of total daily amount of meat protein at baseline (prior to receiving the intervention products) and endline (sixth weeks of receiving the intervention products), (2) change in proportion of meat protein of the total protein intake, and (3) counts of dinner meals with meat and alternative protein products during baseline week 0 and during each of the intervention weeks, including the endline assessment during the 6th week of intervention.

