## Materials and methods

### Study design

The study is a two-arm randomized equivalence intervention trial. The participants are recruited from families. In each family, one adult and one 8–10 year-old child are enrolled as paired participants. The families are provided products incorporating alternative proteins (insect-based or plant-based) suited to replace meat in dinner meals three times per week, for 6 weeks.

Figure 1 depicts the study flowchart. Recruitment, information meetings, collection of informed consent, and other relevant duties are conducted by the on-site project management team and supervised by the PI. During the recruitment period, interested parents and children will attend an information meeting at the Department of Nutrition, Exercise and Sports of the University of Copenhagen, formally enrolling to participate when signing consent. Subsequently, participants receive instructions for baseline measurements. Baseline measurements are completed during the following week, to estimate habitual protein intake (urine and dietary registrations), food neophobia (questionnaire), food disgust (questionnaire), and previous exposure to edible insects (questionnaire). Participating adults will complete a household characteristics questionnaire and a meat attachment questionnaire. One week later, the participants are returning to the department for random allocation to experimental diets, and distribution of products for the following 2 weeks. During that visit, anthropometric measurements will be collected prior to the start of the dietary intervention. Daily food records (questionnaire) will start during the first week of the dietary intervention up to the final day of the dietary intervention. Intervention week 1 includes the baseline food acceptability and feedback questionnaire, to be completed by the participating adult and child. Intervention week 5 includes the endline food acceptability and feedback questionnaire. During intervention week 6, the paired participants will collect endline urine samples and complete the endline 4-day dietary registrations and end-of-study questionnaires. To aid with retention, reminders are sent to participants to complete the registrations, questionnaire, and prior to appointments.

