### Study participants

#### Inclusion criteria

Participants must be healthy, which is determined from the self-reported medical history. All medication that is necessary for the participant’s health or a medical condition and which is not listed in the exclusion criteria may be continued during the study.

Participants must eat meat for dinner at least 5 days a week on average and be willing to consume both insect- and plant-based foods. Participants must be able to talk, read, and understand Danish to properly understand the study procedures.

Adults must have basic computer competency and the household must have freezer capacity for 2 weeks of food.

Children must be between 8 and 10 years old. If a child wants to participate, but their custody holder does not want to participate, another adult from the household can participate with the child. The custody holder is still responsible for the child’s participation in the study.

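### The hypothesised 20% is set on 14 meals a week, but the only meal-count endpoint is dinners (at most 7); read on that count, 20% is half as demanding

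*Protocol article*

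**What the plan says.** All places are in the protocol article.

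- **Objective and hypothesis** sets the 20% as a share of meat protein over a week and assumes that meat is eaten mainly at lunch and dinner.
- **Portion sizes** assumes that meat is split equally between those two meals (13.4 g of meat protein per meal for adults, 9.7 g for children). Each of three dinner portions a week is sized to replace that meal's meat completely. **Study design** describes the products as "suited to replace meat in dinner meals three times per week, for 6 weeks".
- **Statistics** writes the 20% as a change "from *x̄* = 14 meals/week to *x̄* = 11.2 meals/week, we will need a sample size of 78 paired participants". It then analyses "changes in meal patterns as counts of meals with meat and the total protein intake at baseline and endline", "hypothesizing no change in total protein intake and 20% replacement of the meat meal using linear models".
- **Primary outcome** defines co-primary (3) as "counts of dinner meals with meat and alternative protein products during baseline week 0 and during each of the intervention weeks". **Daily food records** asks about meat at dinner only.
- **Inclusion criteria** gives the baseline level: "Participants must eat meat for dinner at least 5 days a week on average".

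No section gives a separate target for the dinner count, and Statistics does not say which meals make up the 14.

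**The concern.** The only quantified target for the primary outcome is a percentage derived on a 14-meal week. The analysis sentence attaches it to a meal count, and the meal count defined as an endpoint runs from 0 to 7. The same percentage therefore stands for two different amounts of replacement, depending on the base the reader supplies.

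At stake is how the results are described. A menu that displaces meat at only half of its dinners could be reported as having replaced 20% of meat meals, while the same behaviour falls well short of the 20% of weekly meat protein that the hypothesis is about. The point concerns the meaning of the 20% on co-primary (3). It does not concern the number of families to recruit.

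**Working it through.** **Inputs.** Meal base 14, target 11.2, SD 7, alpha 0.05 and power 0.80 (printed as β) from Statistics; 3 portions a week from Study design; 13.4 g and 9.7 g per meal from Portion sizes; dinner-only count from Primary outcome; at least 5 meat dinners a week from Inclusion criteria.

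**1. The plan's own figure.** The difference is 14 − 11.2 = 2.8, and 2.8/14 = 20%. For a one-sided test of a within-arm change, n = (7 × (1.645 + 0.842)/2.8)² = 38.7, so 39 per arm and 78 over two arms. The one-sided two-sample form doubles this to 77.3, so 78 per arm. The two-sided forms give 50 and 99 per arm and do not reproduce 78. Sidedness is a separate matter; what counts here is that 78 rests on 2.8 meals, and so on the 14-meal base.

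**2. Where 14 comes from.** Lunch and dinner on seven days is 2 × 7 = 14. Three fully replaced dinners are 3/14 = 21.4% of these. In protein:
- adults: 3 × 13.4 = 40.2 g of 14 × 13.4 = 187.6 g, or 21.4%
- children: 3 × 9.7 = 29.1 g of 14 × 9.7 = 135.8 g, or 21.4%

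This fits the design target of 20%, but it is an inference, because Statistics does not label the 14.

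**3. What 20% requires on each base**, for a person with 7 meat dinners and 14 meat meals a week:

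| Base | 20% of base | Share of the 3 portions that must displace meat |
|---|---|---|
| 14 meals | 0.20 × 14 = 2.8 | 2.8/3 = 93% |
| 7 dinners | 0.20 × 7 = 1.4 | 1.4/3 = 47% |

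**4. One behaviour, two readings.** If half the portions displace meat, 1.5 meals a week lose it. Meat dinners fall by 1.5/7 = 21.4%. Weekly meat meals, and meat protein under the equal split, fall by 1.5/14 = 10.7%. Conversely, a fall of exactly 20% in dinners is 1.4/14 = 10% of weekly meat meals, half the hypothesised amount.

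**5. The other reading of 14.** If 14 meant 7 dinners for each of the two paired members, six portions would be supplied and 2.8/6 = 47% would have to displace meat. Over the pair's 28 lunches and dinners that is 2.8/28 = 10%. The 20% would then already be a dinner figure, out of line with the weekly protein hypothesis. The twofold gap does not depend on which reading is right.

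**The case against.** - **Statistics says meals, not dinners.** This stands. The sentence never explicitly applies 20% to dinners, and the nearest base is the 14 in the paragraph before. A reader might infer that the protocol has set a weaker dinner target. The text does not support that; it leaves the base open. The difficulty remains because the endpoint to which a meal-count hypothesis would attach is defined on dinners.
- **Lunch could be counted.** The complete 4-day registrations at baseline and endline could supply lunch data, so a lunch-plus-dinner count at those two times is conceivable. But no such count is defined as an endpoint, and co-primary (3) is also wanted in each intervention week, where the record covers dinner only.
- **The 20% is not a success rule.** This also stands. A reader might infer that co-primary (3) would be declared met at 20%. No rule in the article does so, and meat protein is itself co-primary (1) and (2), so a shortfall there would be visible.
- **A starker contrast is tempting.** For someone at the eligibility minimum of 5 meat dinners, 20% is 1.0 dinner, or 33% of the portions. Setting that against 93% compares different people. With 5 meat dinners and at most 7 meat lunches, the person has at most 12 meat meals, and 20% is at most 2.4, or 80% of the portions; with 5 lunches it is 2.0, or 67%. Only comparisons at the same baseline are fair.
- **The full protocol or analysis plan may settle the base.** It may. The point is not that detail is missing: the article itself states the 20%, attaches it to meal counts and defines the count on another base.

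**Conclusion.** The mismatch is real, and it is one of base, not of miscalculation: each figure in the article is consistent with its own base. If the hypothesised 20% is read on the dinner count, a person with 7 meat dinners reaches it when 47% of the portions displace meat, against 93% on the 14-meal base, so replacement would be overstated about twofold. This rests on three assumptions: the 14 is lunch plus dinner for one person (inferred), meat is split equally between the two meals (the plan's assumption), and meat is displaced only at the dinners for which products are supplied. The data and endpoints remain valid; what needs repair is the benchmark attached to co-primary (3).

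**What to change.** In Statistics, tie the 20% hypothesis to weekly meat protein. That is co-primary (1). It also covers co-primary (2) if total protein is maintained as hypothesised, since a 20% fall in the numerator over an unchanged denominator is a 20% fall in the proportion.

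For co-primary (3), report the change in meat dinners per person per week with its confidence interval, and attach no 20% claim. If a reference value is wanted, state it in dinners and name its assumptions: 2.8 a week is 40% of 7 dinners, and full displacement by all three portions is 3/7 = 43%. The 2.8 holds only if 14 is one person's lunches and dinners, and it would be 2.8/5 = 56% for a participant with 5 meat dinners.

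The change is a sentence or two and needs no new data. Its cost is that the count endpoint either loses its 20% benchmark or, with a dinner-scale reference, becomes harder to meet.

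### Spearman's rho is planned as the test of before-after change in neophobia, exposure and disgust, but it measures rank agreement and cannot test change

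*Protocol article*

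**What the plan says.** The Statistics section assigns one method to the perception scales: a Spearman's "rho test will be used to assess perception change (neophobia, exposure, and disgust) before and after the intervention". The next sentence handles another before-after comparison differently. For urine, a paired-sample t "test (or Wilcoxon test, if not normally distributed) will be used to analyze pre- and post- intervention urine samples".

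On timing, the Study design section lists the neophobia, disgust and exposure questionnaires among the baseline-week measurements. The section on exposure to edible insects says that its questionnaire "is specific to insect-based foods but will be administered to all participants prior to randomization". In week 6 the pairs are to "collect endline urine samples and complete the endline 4-day dietary registrations and end-of-study questionnaires". The section on the end-of-study questionnaire describes its content: "The end-of-study questionnaire will record participant attitude towards alternative proteins and the study products post intervention". It also mentions feedback on how the study was organised, but does not name the three scales.

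On role, the Secondary outcome section lists neophobia, disgust and earlier exposure as explanatory variables. The Primary outcome section does not mention them.

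**The concern.** The stated aim is to learn whether perception changed. Spearman's rho tests a different hypothesis: whether a person who ranks high before also tends to rank high after. If nobody changes, rho is 1. If everybody falls by one point, rho is again 1. A significant rho therefore shows stable ranking, and a non-significant rho does not show that the average stayed put.

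If the plan is followed literally, a scale that measures a stable trait tends to give a significant result whether or not the intervention did anything, and that result could be taken for a change in perception. A real fall in disgust or neophobia would leave no trace in the statistic.

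There is a second, smaller matter. The test needs scores from after the intervention, and the readable text names these scales only at baseline.

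**Working it through.** The plan gives no figure for this analysis, so there is none to reproduce. The check is of what the named test does.

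**Inputs.** From the Statistics section: 78 pairs and alpha 0.05. Assumed: two-sided testing (the section does not state sides), 78 before-after observations (for example, the adults), normal scores, before-after correlations of 0, 0.3, 0.6 and 0.8, and a true shift of 0 or 0.5 SD. The documents give no correlation or shift.

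**Step 1: invariance.** Rho is computed from ranks. Subtracting the same amount from every endline score leaves the ranks, and so rho and its p-value, as they were. In one simulated data set of 78 pairs, the endline scores were lowered by a fixed amount:

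| Endline lowered by (points) | rho | Spearman p | Wilcoxon signed-rank p |
|---|---|---|---|
| 0 | 0.492 | 4.9e-06 | 0.49 |
| 0.5 | 0.492 | 4.9e-06 | 4.7e-07 |
| 1 | 0.492 | 4.9e-06 | 1.4e-12 |
| 2 | 0.492 | 4.9e-06 | 1.7e-14 |

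**Step 2: rejection rates**, 3000 simulated trials per row:

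| Correlation | True shift (SD) | Spearman rejects | Paired t rejects |
|---|---|---|---|
| 0 | 0 | 6.0% | 4.4% |
| 0 | 0.5 | 5.3% | 86.5% |
| 0.3 | 0 | 72.4% | 5.2% |
| 0.3 | 0.5 | 71.5% | 95.7% |
| 0.6 | 0 | 100% | 5.0% |
| 0.6 | 0.5 | 100% | 99.8% |
| 0.8 | 0 | 100% | 5.3% |
| 0.8 | 0.5 | 100% | 100% |

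The Spearman column follows the correlation and ignores the shift; the small differences within each correlation are simulation error. The paired t column holds its level when nothing changes and responds when something does.

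**Step 3: check by formula at correlation 0.3.** For normal data the Spearman correlation is (6/π) × arcsin(0.3/2) = 0.288. Its Fisher transform is 0.296, with standard error √(1.06/75) = 0.119. The ratio is 2.49, and the rejection rate is about Φ(2.49 − 1.96) = Φ(0.53) = 70%, close to the simulated 72%. For the paired t at the same correlation and a 0.5 SD shift, the SD of the difference is √(2 × 0.7) = 1.183, so the expected statistic is (0.5/1.183) × √78 = 3.73. Power is about Φ(3.73 − 1.96) = 96%, which agrees with 95.7%.

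**Step 4: smaller n.** If rho were computed within each arm, with 78/2 = 39 observations, the standard error becomes √(1.06/36) = 0.172. At correlation 0.3 with no change the rate is Φ(0.296/0.172 − 1.96), about 41%. At 0.6 the Spearman correlation is 0.582, its transform 0.665, and the rate about 97%. Splitting by arm lowers the rate but does not turn rho into a test of change.

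**The case against.** The choice of test has no good defence. One could suppose that rho was meant to relate change to some other variable, but the sentence names none and gives before-after change as its purpose. The objections that carry weight concern how far the point extends.

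- **Timing.** A reader might infer that no after-measurement is scheduled. The documents do not support that. The Study design section has end-of-study questionnaires in the plural, with contents not listed; the sections on neophobia and disgust give no timing; the flowchart is not shown; and the article condenses a fuller protocol. The Statistics sentence itself implies that a repeat is intended. What stands is that no readable section names one.
- **Treatment arm.** A reader might also infer that the analysis ignores randomisation. The sentence is silent on whether rho is pooled or computed by arm, and no between-arm objective is stated for these scales. This is not a fault that the text shows.
- **Size.** A flat statement that the test is always significant would rest on one chosen correlation. At 0 the rate is about 5-6%; it rises with the correlation. The normal model also fits the exposure questionnaire poorly, since participants pick one statement there. The invariance in Step 1 needs no such model.
- **Importance.** The scales are neither primary nor secondary outcomes, and the sample size does not depend on them. This stands and limits the severity.

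**Conclusion.** The planned test is wrong for its stated purpose. That conclusion needs no assumption, because rho is unchanged by a common shift. How often it would wrongly suggest change depends on the before-after correlation, which is assumed here: with 78 pairs and no true change, about 5-6% at 0, about 72% at 0.3 and about 100% at 0.6 or more, against about 5% for a paired test. In the other direction, with a true 0.5 SD change and correlation 0, rho rejects in 5.3% of trials and the paired t in 86.5%.

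The timing of the scales is a matter for reconciliation, not a demonstrated omission. Severity is moderate: the primary outcome (meat protein and dinner counts) and the secondary outcome (liking) are not affected.

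**What to change.** 1. In the Statistics section, replace Spearman's rho with a paired test of change: Wilcoxon signed-rank, or paired t where the scores allow it, as already planned for urine. Report the change with a confidence interval.
2. Analyse adults and children separately. Neophobia is measured with different instruments in the two groups, and disgust with different response scales.
3. For any between-arm comparison, regress the endline score on arm with adjustment for the baseline score.
4. State when each scale is given after the intervention, and reconcile the Secondary outcome, Study design, exposure and end-of-study questionnaire sections with the before-after wording under Statistics. If the scales are not repeated, drop the before-after claim and keep them as explanatory variables.

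Items 1 to 3 cost a sentence or two and need no new data if the scales are already repeated. Adding scales now would cost more: the Trial status section reports recruitment from August 2022, so families who have finished cannot give an endline score on schedule, and it sends protocol changes to the ethics committee as an amendment. If no repeat exists, dropping the claim is the cheaper course.
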